### Random Allocation Procedure

Patients were randomly assigned to one of the two treatment groups with an equal probability of assignment to each treatment (allocation ratio 1:1). A centralised randomization procedure was employed. The trial biostatistician prepared the sequence of treatments randomly permuted in blocks of constant size. The site investigators did not know the block size. The allocation was stratified by living condition (residential facility versus all the other living conditions) because in patients with resistant schizophrenia this hard variable may be considered a proxy of severity of illness. Recruiting physicians were asked to contact an operator at the World Health Organisation Collaborative Centre of the University of Verona. The operator had access to a computerised system that provides, after information on the enrolled participant was entered, the patient's identification number (ID) and the allocated treatment. The operator had not access to the randomisation lists. This procedure of randomisation was developed to fully conceal treatment allocation [41].

### Statistical consideration

The statistical analysis will be masked, i.e. the trial biostatistician will be blinded to the treatment groups until the analysis has been completed. Moreover, the trial biostatistician will not be involved in determining patients' eligibility, in administering the treatment, in measuring the outcomes or in entering data.

Two data locks will occur during the study. The first one will happen 3 months after the end of the enrolment period, when the information on the primary endpoint and on the short-term secondary endpoints will be available for all the participants. The second one will happen at the end of the study (12 months after the end of the enrolment period), when information on the long-term secondary endpoints will be available for all participants. Accordingly, two data analyses will be performed on an intention-to-treat (ITT) basis. All randomised participants who will receive at least one dose of the investigational drugs will be included in the ITT analysis. The outcomes of patients included in the non-randomized cohort will be presented descriptively. No formal statistical analysis has been planned to compare the randomized participants and the eligible, non-randomized patient cohort.

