## Design and Methods

### Design of The Clozapine Haloperidol Aripiprazole Trial (CHAT)

The principal clinical question to be answered by CHAT is the relative effectiveness and tolerability of combination treatment with clozapine plus aripiprazole compared to combination treatment with clozapine plus haloperidol in patients with an incomplete response to treatment with clozapine over an appropriate period of time. CHAT is a prospective, multicentre, randomized, parallel-group, superiority trial that follows patients over a period of 12 months. Consecutive patients meeting the trial entry criteria were randomly assigned to combination with aripiprazole or haloperidol. These patients constituted the randomised cohort (Figure 1). Patients meeting the trial entry criteria that were not randomly assigned to competitive treatments were followed under real-world circumstances. These patients constituted the observational cohort (Figure 1). In both the experimental and observational cohort patients and clinicians were not blind to pharmacological treatments provided during the trial. Patients will be assessed at baseline, at 3, 6 and 12 months using the instruments reported in Figure 2.

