### Primary outcome

Withdrawal from allocated treatment within 3 months is the primary outcome. This outcome was selected because stopping or changing antipsychotic combination treatment is a frequent occurrence and major problem in the treatment of patients with schizophrenia. In addition, according to Lieberman and colleagues, this measure integrates patients' and clinicians' judgments of efficacy, safety, and tolerability into a global measure of effectiveness that reflects their evaluation of therapeutic benefits in relation to undesirable effects [21].

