### Power analysis for sample size calculation

At the time of development of the CHAT, only one antipsychotic trial employed discontinuation by any cause as the primary endpoint [21]. On the basis of this trial, it was initially hypothesised a withdrawal proportion from allocated treatment within 3 months (primary study endpoint) of 25% in the group treated with clozapine plus haloperidol (control group). Moreover, it was hypothesised that the augmentation with aripiprazole (experimental group) would show a clinically significant advantage by producing a withdrawal proportion of 10%. A sample size of 194 patients (97 in each group) was chosen since it achieves 80% power to detect a difference of 15% between the two withdrawal proportions. The test statistic used was the two-sided Z test with pooled variance. The significance level of the test was targeted at 5%. Having assumed that 10% of the participants could be lost within 3 months, or could not provide valid data at month 3, the target total sample size for CHAT was 216 (= 194/0.90) patients in order to obtain 194 evaluable subjects [39,40].

Having considered the possibility that the target sample size could not be reached, we anticipated that the total sample size at the end of the enrolment period would be around 100 patients. With such a total sample size, CHAT achieves 80% power to detect a difference of 20% between the two withdrawal proportions (25% in the group treated with clozapine plus haloperidol versus 5% in the group treated with clozapine plus aripiprazole).

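### The set labelled intention-to-treat requires a first dose, so in this open-label trial it can drop patients who never start, the earliest withdrawals from allocated treatment

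*Protocol article*

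**What the plan says.** Under Statistical consideration, the protocol article says of the two data locks that "two data analyses will be performed on an intention-to-treat (ITT) basis". The next sentence defines the set: "All randomised participants who will receive at least one dose of the investigational drugs will be included in the ITT analysis".

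Three other parts of the article bear on this rule:

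- **Primary outcome:** "Withdrawal from allocated treatment within 3 months is the primary outcome". The reason given is that "this measure integrates patients' and clinicians' judgments of efficacy, safety, and tolerability into a global measure of effectiveness".
- **Design of CHAT:** "In both the experimental and observational cohort patients and clinicians were not blind to pharmacological treatments provided during the trial".
- **Random Allocation Procedure:** the recruiting physician contacts a central operator, whose system returns the patient number and the allocated treatment. The physician thus knows the arm before any dose is given.

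Analysis of the Primary Outcome compares the proportions withdrawing by a chi-square test, with risk ratios in support. The article gives no analysis of all randomised patients and does not say how a patient who never starts the allocated drug is counted.

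**The concern.** A first-dose condition can be nearly harmless in a blinded trial, where failure to start is unlikely to depend on the arm. Here both parties know the allocation, so declining the drug, or deciding not to prescribe it, can be a response to it. It is also the kind of patient and clinician judgement that the endpoint was chosen to capture.

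A patient who never starts is, on the natural reading, the earliest withdrawal from allocated treatment. The rule removes that patient from both numerator and denominator. The sample is then selected after randomisation on an event that overlaps the outcome, and the comparison loses the protection of randomisation.

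The primary test and the risk ratio are at stake. So are 12-month withdrawal and time to withdrawal, because the same set serves both data locks. Masking the biostatistician does not help, since the selection takes place at the sites.

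**Working it through.** **Inputs from the protocol article**

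- Withdrawal of 25% (haloperidol) and 10% (aripiprazole), two-sided pooled Z test at 5%, 97 per arm for 80% power; the fallback is 25% v 5% with about 100 patients (Power analysis for sample size calculation).
- 1:1 allocation (Random Allocation Procedure).
- 106 patients recruited (Status of the trial).

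**Assumptions**

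- 53 patients per arm; the article does not give the arm sizes.
- The number of never-dosed patients is not given, so a range is shown.
- In the all-randomised set, a never-dosed patient counts as withdrawn.

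**The plan's own figures.** The article states: "A sample size of 194 patients (97 in each group) was chosen since it achieves 80% power to detect a difference of 15" percentage points. The pooled normal approximation gives 99.5, so 100 per arm, and 79.0% power at 97. The unpooled formula gives 96.8, so 97. Exact enumeration of the pooled Z test gives 80.2% at 97. Allowing for 10% loss, 194/0.90 = 215.6, so 216. For the fallback, 50 per arm gives 80.9%. The sample sizes reproduce and are not in dispute.

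**Step 1: effect on the primary test.** For a 2×2 table with cells a, b, c, d and total N, the uncorrected chi-square is N(ad − bc)² divided by the product of the four margins. Take 13/53 (24.5%) v 5/53 (9.4%), close to the planning rates.

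- All randomised: 106 × (13×48 − 40×5)² / (53×53×18×88) = 106 × 424² / 4,449,456 = 4.28, p=0.039.
- One never-dosed haloperidol patient dropped: 105 × (12×48 − 40×5)² / (52×53×17×88) = 105 × 376² / 4,122,976 = 3.60, p=0.058.

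The same formula gives:

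| Never-dosed patients dropped | Haloperidol | Aripiprazole | p |
|---|---|---|---|
| None | 13/53 | 5/53 | 0.039 |
| 1 haloperidol | 12/52 | 5/53 | 0.058 |
| 2 haloperidol | 11/51 | 5/53 | 0.086 |
| 3 haloperidol | 10/50 | 5/53 | 0.129 |
| 1 aripiprazole | 13/53 | 4/52 | 0.019 |
| 2 aripiprazole | 13/53 | 3/51 | 0.008 |
| 3 aripiprazole | 13/53 | 2/50 | 0.003 |
| 2 in each arm | 11/51 | 3/51 | 0.021 |

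Equal exclusions do not leave the result unchanged either.

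Starting instead from 14/53 v 5/53 (p=0.023), dropping one, two or three haloperidol never-starters gives p=0.034, 0.052 and 0.078. Dropping one aripiprazole never-starter gives 14/53 v 4/52, p=0.011.

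**Step 2: effect on power.** If a fraction f of an arm with true withdrawal p never starts and is dropped, the analysed rate is (p − f)/(1 − f) and the arm shrinks to 53(1 − f).

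- 25% v 5%, haloperidol arm only: power is 83.2% at f=0, then 78.2%, 72.1%, 65.0% and 47.8% at f=2%, 4%, 6% and 10%.
- 25% v 10%, with 5% of haloperidol and 1% of aripiprazole patients never starting: the analysed rates are 0.20/0.95 = 21.1% and 0.09/0.99 = 9.1%, and power falls from 53% to about 39–40%.
- 25% v 10%, with 1% never starting in each arm: 0.24/0.99 = 24.2% v 9.1%, and power rises slightly to about 55%.

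**Step 3: type I error.** Let true withdrawal be 25% in both arms, with never-dosed patients dropped from one arm only. At f=4%, for example, that arm is analysed at (0.25 − 0.04)/0.96 = 21.9%. The two-sided rejection rate is 5.0% at f=0, 6.6% at 4%, 8.8% at 6% and 17.3% at 10%.

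**The case against.** The strongest reply is that the article does not show that the rule excludes anyone. It gives no count or expected rate of never-dosed patients, and the 10% loss allowance concerns month-3 data. If every randomised patient took one dose, the two sets are the same. Separate criteria for random allocation, an observational cohort for those who did not meet them, and free choice of starting dose may all keep non-starting rare. This stands as a limit on size. It does not justify the rule, because an analysis set has to be right before the data are seen.

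Second, the direction is open. Scenarios in which only haloperidol patients fail to start show one side; the reverse moves p the other way. This also stands, and both directions are shown above.

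Third, the article explains the endpoint in terms of stopping or changing the combination, and a patient who never began it has arguably done neither. Counting non-starting as withdrawal is a reading, though the natural one for withdrawal from allocated treatment. However these patients are counted, leaving them out is not intention-to-treat.

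Fourth, the investigational drugs are not defined, and the section on Italian legislation lists clozapine among the trial's drugs. If clozapine counted, patients already taking it would all qualify and the condition would exclude nobody. That reading empties the rule of meaning; the added drug is the sensible one.

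Finally, a statistical analysis plan not shown may add an analysis of all randomised patients. The set stated here would still contradict its label.

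**Conclusion.** The concern holds. The article states a first-dose condition under an intention-to-treat label. With open allocation and an endpoint of withdrawal from allocated treatment, the condition can select on the outcome after randomisation. Following the plan as written can bias the primary test in either direction.

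The actual size is unknown. At 53 per arm, with 18 events in the illustration, a single excluded patient can move p across 0.05 (0.039 to 0.058). One-sided exclusion of 4% to 10% raises the type I error to between 6.6% and 17.3% when there is no true difference. These figures rest on three assumptions: equal arms, the illustrative event counts and never-dosed fractions, and the reading that non-starting is withdrawal. If no randomised patient went undosed, the effect is nil.

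**What to change.** Define the intention-to-treat set as all randomised patients, analysed in the arm to which they were allocated. State that a patient who never starts the allocated added drug counts as withdrawn at day 0 for the 3-month, 12-month and time-to-withdrawal outcomes. Keep the set with at least one dose as a sensitivity analysis, labelled modified intention-to-treat, and say that the dose meant is of the allocated added drug. Report the number never dosed in each arm.

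The cost is a short change of wording before the first data lock, or at the latest before unmasking. The central randomisation system already identifies every randomised patient, so no new data are needed.

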### Analysis of the Primary Outcome

In the randomized cohort, the proportion of patients withdrawing from the assigned treatment within 3 months will be compared between the two groups of treatment through the chi-square test. Additionally, we will calculate risk ratios and their 95% confidence intervals to corroborate the main analysis. A multivariate analysis (secondary analysis) will be performed through a Poisson regression model with a robust error variance, given that this procedure allows to estimate relative risks directly [42].

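### Allocation is stratified by living condition but the primary chi-square test is not: a valid test that may lose a little power, which a stratified test would recover at no cost

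*Protocol article*

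**What the plan says.** All references are to the protocol article.

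- **Random Allocation Procedure:** "The allocation was stratified by living condition (residential facility versus all the other living conditions"). The reason given is that "this hard variable may be considered a proxy of severity of illness". Allocation is 1:1 in permuted blocks of constant size.
- **Analysis of the Primary Outcome:** the proportions withdrawing within 3 months "will be compared between the two groups of treatment through the chi-square test". Risk ratios with 95% confidence intervals support this result. No stratification is named for either. A robust Poisson regression follows and is labelled secondary.
- **Power analysis for sample size calculation:** "The test statistic used was the two-sided Z test with pooled variance", at a 5% level. "A sample size of 194 patients (97 in each group) was chosen since it achieves 80% power to detect a difference of 15" percentage points, that is 25% v 10%. A reduced scenario of about 100 patients is given 80% power for 25% v 5%.
- **Status of the trial and expected achievements:** 106 patients were recruited against a target of 216, and recruitment is closed.

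**The concern.** Blocking within strata forces the arms to be nearly balanced on living condition. If living condition is related to withdrawal, that balance removes part of the chance variation in the difference between arms. The plain chi-square test does not know this. Its variance still contains the between-stratum part, so it is larger than the true variance of the difference. The test then rejects a true null hypothesis less often than 5% of the time and has less power than the same data could give.

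What is at stake is efficiency only. With 106 of 216 patients (106/216 = 49%) and recruitment closed, the choice of analysis is one of the few ways left to use the data better.

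**Working it through.** **1. The article's own figures.** Inputs: 25% v 10%, two-sided 5%, 80% power, all from the power section.

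- Unpooled variance: n = (1.960 + 0.842)² × (0.25×0.75 + 0.10×0.90) / 0.15² = 7.849 × 0.2775 / 0.0225 = 96.8, so 97 per arm. This is the stated figure.
- Pooled variance, as the text describes: n = [1.960√(2×0.175×0.825) + 0.842√0.2775]² / 0.15² = 99.5, so 100 per arm. At 97 per arm the power is 0.790. The gap of about one point is not material.
- 194/0.90 = 215.6, so 216.
- 25% v 5% with 50 per arm: power 0.809.

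The stated figures hold. They rest on an unstratified test, which is the same test as the uncorrected chi-square.

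**2. How conservative the chi-square test can be.** Let f be the share in residential facilities, p₁ and p₀ the withdrawal rates in the two strata, and p the overall rate. Under the null hypothesis, with balance within strata,

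true variance / chi-square variance = 1 − f(1−f)(p₁−p₀)² / [p(1−p)].

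Example with p = 0.25, f = 0.3 and odds ratio 5: p₀ = 0.153 and p₁ = 0.475. The ratio is 1 − 0.21×0.322²/0.1875 = 0.884. The critical value becomes 1.96/√0.884 = 2.085, giving a type I error of 0.037 (0.039 by simulation).

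**3. Simulation at N = 106.** The article does not give f, the odds ratio of living condition on withdrawal, or the block size. Assumed: f = 0.3 and 0.5, odds ratios 1 to 10 (the same in both arms), blocks of 4, and 200,000 trials per scenario. The chi-square and CMH tests are both uncorrected. Ranges cover the two values of f.

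| Odds ratio | Type I error, chi-square | Type I error, CMH | Power 25% v 10%, chi-square | Power 25% v 10%, CMH | Power 25% v 5%, chi-square | Power 25% v 5%, CMH |
|---|---|---|---|---|---|---|
| 1 | 0.052 | 0.050 | 0.540–0.542 | 0.539–0.540 | 0.861 | 0.862 |
| 2 | 0.049–0.050 | 0.049–0.050 | 0.539–0.540 | 0.543–0.544 | 0.862–0.863 | 0.866 |
| 3 | 0.046 | 0.049–0.050 | 0.539–0.541 | 0.554 | 0.864 | 0.872 |
| 5 | 0.039–0.040 | 0.049–0.050 | 0.541–0.543 | 0.570–0.576 | 0.867–0.869 | 0.881–0.886 |
| 10 | 0.028–0.033 | 0.049 | 0.542–0.544 | 0.591–0.618 | 0.873–0.877 | 0.894–0.908 |

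Power given up by the chi-square test, in percentage points:

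- 25% v 10%: 0.4 at odds ratio 2, 1.3 to 1.5 at 3, 2.7 to 3.5 at 5, and 4.9 to 7.4 at 10.
- 25% v 5%: 0.3 to 0.4 at 2, 0.8 at 3, 1.4 to 1.7 at 5, and 2.1 to 3.1 at 10.

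**4. Extreme strata, for scale.** Two cases with overall rates of 25% v 10%, 400,000 trials each:

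- Equal strata with control rates 5% and 45% (odds ratio (0.45/0.55)/(0.05/0.95) = 15.5) and experimental rates 2% and 18%: power 54.3% v 60.1% for CMH, a loss of about 6 points.
- 30% of patients at 60% and 70% at 10% (odds ratio 13.5), with experimental rates 24% and 4%: power 54.3% v 62.5%, a loss of about 8 points.

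**5. Against under-recruitment.** By the pooled formula, going from 97 to 53 per arm lowers power for 25% v 10% from 0.79 to 0.53, a fall of 26 points.

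**The case against.** The strongest reply is that nothing in the article is wrong. The trial was sized on an unstratified test and is analysed with the same test. That test is valid, since ignoring a stratification factor can only make it conservative, and balance within strata leaves no evident bias in the unadjusted risk ratio. All of this stands.

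A reader might infer that the primary test is conservative and underpowered as a matter of fact. The article does not support that. It says only that living condition may be a proxy of severity; it does not link it to 3-month withdrawal and gives neither rates by stratum nor the share in residential facilities. Losses of 5 points or more need an odds ratio of about 10 or above, and nothing in the article suggests one. Nor does the choice of test explain the low power at 25% v 10%, which comes from recruitment.

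A reader might also fault the secondary Poisson model for not listing its covariates. That is no finding: a condensed article commonly leaves such a list to the full protocol or analysis plan, and neither is shown. Living condition may already be in that model.

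What survives is narrow. The article does fix the primary test, and that test does not use the factor on which allocation was stratified. An adjusted model labelled secondary cannot change the primary p-value.

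**Conclusion.** The mismatch is real and minor. The primary test is valid, but it forgoes whatever precision the stratified allocation provides. For 25% v 10% at N = 106 the loss is negligible at an odds ratio of 2 or below, about 1 to 3.5 power points at 3 to 5, and 5 to 8 points only at 10 or more. For the article's 25% v 5% scenario it stays under 2 points up to an odds ratio of 5. These figures rest on assumed stratum shares, odds ratios and block size.

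The case for changing rests on the lack of a downside. In the main simulations the CMH test held its size at 0.049 to 0.050, and with a non-prognostic factor its power was within 0.2 points of the chi-square test's.

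**What to change.** Before unmasking, and recorded as a dated change:

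- Make the primary test a Cochran-Mantel-Haenszel test stratified by living condition as used at randomisation, without continuity correction. The correction matters: applied to the plain chi-square test at odds ratio 1, it lowers simulated power from about 0.54 to 0.43 (25% v 10%) and from 0.86 to 0.78 (25% v 5%), more than stratification is likely to gain.
- Report the Mantel-Haenszel risk ratio and risk difference with 95% confidence intervals.
- Keep the unstratified chi-square test as a sensitivity analysis.

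The cost is a change of wording in the analysis plan. The stratum had to be known to allocate each patient, so no new data are needed. If an analysis plan not shown here already specifies this, only the article's description differs.

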## Status of the trial and expected achievements

The recruitment phase started on September 1^st ^2006 and finished on December 31^st ^2008. During this period, 38 clinical sites across Italy actively participated in the study and recruited a total of 106 patients. This means that, despite the planned sample size of 216 patients has not been achieved, CHAT is the largest randomised study conducted so far in Western countries on this topic. Data collection, study monitoring and data management are performed by the coordinating centre (University of Verona). All study data are entered in a computerised database and stored by the World Health Organisation Collaborative Centre of the University of Verona. The person entering the data is not involved in determining patients' eligibility, administering treatment, or determining outcome. The correctness and consistency of the data is ensured by the double-entry technique and by a set of electronic and manual edit checks. The consistency of the data between the recruitment and follow-up forms and the computerised database are routinely verified. After each of the two data locks, masked data will be transferred to the Unit of Epidemiology and Medical Statistics of the University of Verona for statistical analysis.

The main achievements of this ongoing projects include the following: (a) the implementation of the CHAT protocol provides evidence that it is possible to create a network of community psychiatric services that accept the idea of using their everyday clinical practice to produce randomised knowledge; (b) the possibility of producing knowledge from the practice of medicine does not necessarily require huge financial support, as long as a pragmatic attitude to the evaluation of competitive treatment strategies is adopted; (c) the multicentre design, nested into everyday clinical practice, has been creating a situation where investigators simultaneously act both as physicians and researchers; (d) the pragmatic attitude employed allowed to randomly allocate considerable number of individuals [43]; (e) the current project, by generating evidence on whether it is clinically useful to combine clozapine with aripiprazole rather than with haloperidol, is expected to provide physicians with a solid evidence base to be directly applied in the routine care of patients with schizophrenia.
